### 8.3 INTERIM MONITORING

Interim monitoring will focus on survey completion, intervention engagement and safety. No interim efficacy analyses will be conducted.

### 8.4 STATISTICAL ANALYSIS PLAN

See <https://osf.io/9g58j> for preregistration of statistical plan, hypotheses and outcomes.

Primary and secondary outcomes will be analyzed using linear mixed effects models with time nested within participant. All randomized participants will be included (i.e., intention-to-treat analyses). Maximum likelihood estimation will be used for missing data. To help determine the best fit for modeling change over time, we will plot outcomes over time by group using loess regression. We will then quantitatively compare the Akaike Information Criterion (AIC) and Bayesian Information Criterion (BIC) of candidate models of linear change, loglinear change, polynomial change, and piecewise linear change in which change over the intervention period is modeled separately from change over follow-up. Primary effects of interest are groupXtime interactions from pre- to post, pre- to 3-month follow-up, and pre- to six month follow-up. We will control for gender and age. Models with and without social desirable responding will be compared and the best fitting model will be used.

Covariates may be centered to aid in model interpretation. Statistical significance will be set at a two-tailed alpha of  $p < 0.05$ , false discovery rate corrected for the 9 inferential tests at post-test (2 primary, 7 secondary outcomes) and the three inferential tests at 6-month follow-up. In addition to statistical significance, magnitude of differences will be estimated using standardized mean differences on continuous outcomes and Odds Ratios on binary outcomes.

Before hypothesis testing, we will use the "careless" package in R to check for patterns of aberrant responding on the survey items. Should evidence for inattentive responding be observed, we will report results with and without affected data removed. Given the expected sample size, we do not expect outliers or high leverage points to be observed but we will use simulation methods to check models for these points. Should high influence points be observed, we will report models with and without them.

Should evidence for data not missing at random be observed (e.g., differential attrition between groups, inability to predict missingness based on observed variables) we will conduct pattern-mixture modeling.

We will examine moderation of intervention effects on primary and secondary outcomes by participants gender, age, employment type and location.

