### Integrating the STH and the HMP.

The Center for Healthy Minds (CHM) and AtentaMente will integrate the STH with the HMP. The resulting ISTH program will be a 12-week intervention that consists of an initial eight-week synchronous and app-supported training, followed by an additional four-weeks of app-only training. Employing the best practices both CHM and AtentaMente have honed over past projects, the synchronous components will be delivered through Zoom and recorded, to allow for asynchronous participant engagement if required, and app implementation will be carried out in accordance with the strategies Hirshberg et al. (2021) used successfully (most important is immediate contact with non-adhering participants). The ISTH has the potential to represent a significant step toward fulfilling the urgent need to support HCP well-being in Mexico and longer-term, Latin America.

The STH and the HMP are well-suited to integration. They are constructed around the same theory of change (Figure 1) and model of well-being (i.e., ACIP model), make use of declarative and procedural learning strategies, and provide instruction in many of the same foundational meditation practices. For example, both interventions employ short lessons that teach the key principles underlying a character strength leading to declarative learning about this strength, and follow declarative learning with guided meditations and exercises tailored to daily life experiences where the strength is practiced and applied (procedural learning). The major work of this integration is synchronizing the scope and sequence of the two programs so that users receive a seamless, uniform program, and constructing a modest amount of new content (4 new “learn” podcasts, eight new guided practices) for the four-week fully remote component of the training.

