## 4. STUDY DESIGN

A two-arm parallel RCT with a wait-list controlled design in which the control group may pursue professional development activities as usual and will receive access to the intervention following the final study assessment nine-months post-randomization. Assessors will be blind to group assignment. Target sample sizes were determined based on power analyses. The unit of randomization is the individual participant. The co-primary outcomes are psychological distress and well-being. Participants will complete assessments at baseline, prior to random assignment, after weeks one, three, five, eight and twelve (i.e., post-intervention), and after weeks 24 and 36. A subset of 510 participants (255 from each condition) will be selected for a dried blood spot substudy in which dried blood samples will be collected at baseline, week 12 and week 24. A subset of 510 participants, ideally overlapping with the dried bloodspot substudy, will be selected for the patient satisfaction substudy in which enumerators assess participants' patients perspectives on their care.

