## **5 STUDY INTERVENTION**

The Integrated Stress Toolbox for Healthcare providers (ISTH) is a 12-week meditation-based well-being training. In weeks 1-8, participants engage in weekly 2-hour class sessions that are recorded and posted on a private Youtube channel. There is a final two-hour session at week 12. In-class learning is augmented and extended through content in a special version of the Healthy

Minds Program smartphone app that participants are asked to use on a daily basis throughout the intervention.

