## 8 STATISTICAL ANALYSIS, SAMPLE SIZE AND POWER CALCULATIONS

### 8.1 DESIGN OVERVIEW

This is a two-arm parallel RCT with a wait-list controlled design in which the control group may pursue professional development activities as usual and will receive access to the intervention following the final study assessment nine-months post-randomization. We will enroll up to 4,000 participants within the recruitment window, which closes on May 21, 2023.

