### **11.5 SAFETY**

#### **11.5.1 Safety Personnel**

In addition to study staff, an on call clinician is available for participants reporting AE, UP or SAE. Several of the intervention instructors are physicians and are able to provide emergency medical care if needed during an intervention session.

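### ISTH is taught in live classes and the wait list attends none, but the model has no class level; if stable classes share any effect, standard errors are understated

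*Protocol*

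**What the plan says.** **Design.** Section 4 of the protocol states: "The unit of randomization is the individual participant". Section 7.1 allocates 1:1 within strata of state and facility tier. The planned total is up to 4,000, so about 2,000 per arm.

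**Delivery.** Section 5 states: "In weeks 1-8, participants engage in weekly 2-hour class sessions that are recorded and posted on a private Youtube channel". A further session follows at week 12, and app use is asked for daily. The background section on integrating the two programmes adds: "the synchronous components will be delivered through Zoom and recorded, to allow for asynchronous participant engagement if required". Section 11.5.1 shows that there is more than one instructor: "Several of the intervention instructors are physicians". Under section 8.1, "the control group may pursue professional development activities as usual", so the wait list attends no study classes.

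**Analysis.** Section 8.4 fixes the model: "Primary and secondary outcomes will be analyzed using linear mixed effects models with time nested within participant". On covariates it says: "We will control for gender and age"; social desirability may be added if the fit improves. Location appears only as a moderator.

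**Power.** Section 8.2 assumes a correlation between repeated measures on the same person (0.50 in the main trial, 0.60 in the substudy). It gives no correlation between people.

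**The concern.** People are randomised one by one, but one arm is then taught in groups. If a class or its instructor does better or worse than average, everyone in that class shifts together after baseline. This is a partially nested design: clustering arises after randomisation, and in the ISTH arm only.

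Nothing in the stated model captures such a shift:

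- A participant random intercept absorbs a person's stable level, which cancels in a pre-to-post contrast. The class shift does not cancel.
- A participant random slope would take up the class variance, but would treat it as independent from person to person.
- Stratifying by state and facility tier balances what exists before randomisation, not what the classes create afterwards.

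The shift therefore falls in the group-by-time interaction, which section 8.4 names as the effect of primary interest. The trial is sized for very small effects, so even a modest understatement of the standard error can decide whether a result is called significant. The planned false discovery rate correction does not help, because it takes the p-values as valid.

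**Working it through.** **1. The plan's own figure.** Section 8.2 states a detectable d of 0.04 for 10 assessments and 0.05 for five (N = 4,000, alpha 0.006, power 0.80, r = 0.50). I used the repeated-measures interaction F test with k assessments, noncentrality f² × N × k / (1 − r), df (k − 1) and (N − 2)(k − 1), and d = 2f.

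- 10 assessments: f = 0.0170, so d = 0.034.
- Five assessments: f = 0.0213, so d = 0.043.

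The stated values follow only if these are rounded up. That is a separate matter. What counts here is that the calculation uses one correlation, within person, and has no class term.

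**2. Inputs for the class effect.**

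- From the protocol: 1:1 allocation, about 2,000 per arm, classes in the ISTH arm only.
- Assumed, because the protocol does not give them: m = 25 or 50 people per class (2,000/25 = 80 or 2,000/50 = 40 classes), stable membership, and ICC 0.01 or 0.02 for the change that the contrast measures.

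**3. Formulas.** With n per arm and variance σ²:

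- ISTH mean: variance (σ²/n) × DE, where DE = 1 + (m − 1) × ICC.
- Wait-list mean: variance σ²/n.
- True variance of the difference over the variance the model assumes: VR = (1 + DE)/2.
- The true standard error is √VR times the reported one.
- Actual level of a nominal two-sided 5% test: 2 × [1 − Φ(1.96/√VR)].

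**4. Results.**

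| m | ICC | DE | VR | SE multiplier | Actual level at nominal 5% | Coverage of 95% CI |
|---|---|---|---|---|---|---|
| any | 0 | 1 | 1 | 1.00 | 5.0% | 95.0% |
| 25 | 0.01 | 1.24 | 1.12 | 1.06 | 6.4% | 93.6% |
| 25 | 0.02 | 1.48 | 1.24 | 1.11 | 7.8% | 92.2% |
| 50 | 0.01 | 1.49 | 1.245 | 1.12 | 7.9% | 92.1% |
| 50 | 0.02 | 1.98 | 1.49 | 1.22 | 10.8% | 89.2% |

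At the 0.006 threshold of section 8.2, the actual level over the same range is 0.0094 to 0.0244.

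**5. Effect on power.** In information terms, 4,000 participants act like 4,000/1.12 = 3,571 down to 4,000/1.49 = 2,685. If the stated d of 0.04 scales with the standard error, it becomes 0.04 × 1.058 = 0.042 to 0.04 × 1.221 = 0.049.

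**The case against.** The strongest reply is that the cluster structure is inferred. The protocol gives no class size, number of classes, rule for class membership or ICC. More than one instructor does not prove separate classes with separate instructors; co-teaching or rotation would fit the text as well. If sessions were large shared broadcasts, or people moved freely between sessions and recordings, there would be no stable class to model. Recordings, daily app use and the mainly app-based weeks 9 to 12 could all weaken a class effect.

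Two technical points also stand. If classes were formed by state, part of a raw class ICC would be variation between states that stratification already balances, so DE would overstate the inflation. And leaving the strata out of the model may widen the intervals somewhat, which works the other way.

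Finally, section 8.4 points to a preregistered plan that is not at hand and might contain a class term. Whether instructors are best treated as random or fixed is also open to argument.

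These points make the conclusion conditional; they do not remove it. Section 8.4 does more than leave a detail open: it names a specific nesting structure, and that structure cannot represent a class effect. If the preregistration does include one, the two texts need to be reconciled.

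**Conclusion.** The point holds in conditional form. If ISTH participants belong to stable classes and any class or instructor effect exists, the model in section 8.4 understates the standard error of the group-by-time contrast and the tests exceed their nominal level. Under the assumed 25 to 50 per class and ICC 0.01 to 0.02, the standard error is too small by a factor of 1.06 to 1.22, and a 5% test runs at about 6% to 11%. These are illustrations, not estimates for this trial.

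Two stronger readings are not supported. A reader might infer that the confidence intervals are certainly too narrow; that needs an ICC above zero, which the protocol neither gives nor implies. A reader might also take a more extreme case, such as 100 per class with ICC 0.05, where DE = 5.95, VR = 3.475 and the actual level is 29%; nothing in the protocol supports pairing a class that large with an ICC that high.

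The plan should be changed on this point, but it does not undermine the design.

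**What to change.** - State in section 5 how classes are formed, how many there are, and whether people stay in one class.
- Record for each ISTH participant the class (session group and instructor) to which they are first allocated, and analyse by that class whatever their attendance, which keeps the comparison by intention to treat. The protocol does not describe class allocation at randomisation, so this variable has to be defined.
- In section 8.4, fit a partially nested mixed model: a class random effect on post-baseline change in the ISTH arm, with each wait-list participant as a singleton. Alternatively, use cluster-robust standard errors by class, with each control as its own cluster.
- State in section 8.2 that the detectable effects assume no class effect.

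The cost is one linking variable and some wording, with slightly wider intervals if class effects exist. The protocol mentions no class records, so their availability has to be confirmed. If class effects are negligible, the results will barely move, and the report can show it.

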### 8.2 SAMPLE SIZE AND POWER ANALYSES

Our target sample size was informed in part by our agreements with State Ministers of Health, which requested a minimum number of participants from each participating state. Because of the large, planned sample size (up to 4,000), we conducted two power analyses. First, we conducted a sensitivity power analysis to determine the smallest detectable effect based on the lower bound of the expected intention-to-treat sample of 4,000. To ensure our power estimates were conservative, we based power calculations off of the Bonferroni corrected two-tailed p-value assuming that all primary and secondary outcomes in the parent trial share the same family-wise error 0.05 error rate. We plan to test a total of 9 primary and secondary outcomes for a Bonferroni corrected error rate of 0.006. For measures collected at all 10 assessments points, we assume:

- 0.80 power
- A correlation of  $r = .50$  between the same measure at different assessments
- Error rate of 0.006

Under the above conditions, we will be able to detect a significant group by time interaction effect of Cohen's  $d \geq 0.04$ . For measures assessed at five of the timepoints, assuming the same conditions listed above, we will be able to detect between group effects of Cohen's  $d \geq 0.05$ .

We conducted a second power analysis to determine the size of the randomly selected biomarker and patient satisfaction report subsample required to detect a pre- to post-test change of  $d \geq 0.15$ . We selected  $d \geq 0.15$  as our expected effect size because, in two meta-analyses on the topic of mindfulness-based interventions effects on inflammation,  $d \geq 0.15$  was the smallest observed average effect size on the cytokines we will assay. We assume:

- 0.90 power
- A correlation of  $r = .60$  between the same measure at different assessments
- Error rate of 0.005

In order to detect a statistically significant group by time interaction effect of Cohen's  $d \geq 0.15$  on our measures of peripheral inflammation, we will require a subsample of 468 participants. Assuming 10% of selected participants do not provide a pre-test sample, we plan to randomly select 255 participants from each group (510 total) to participate in biomarker data collection.

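### The form of time in the confirmatory model is chosen from outcome data seen by arm, so the week-12, week-24 and week-36 contrasts are not fixed in advance; a prespecified categorical-visit model fixes them at a modest loss of precision

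*Protocol*

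**What the plan says.** Protocol section 8.4 specifies linear mixed models on all randomized participants and then describes how the form of time will be found. The first step is graphical: "To help determine the best fit for modeling change over time, we will plot outcomes over time by group using loess regression". The second is numerical: "We will then quantitatively compare the Akaike Information Criterion (AIC) and Bayesian Information Criterion (BIC) of candidate models", the candidates being "linear change, loglinear change, polynomial change, and piecewise linear change in which change over the intervention period is modeled separately from change over follow-up". A model with visit as a categorical factor is not among them. The degree of the polynomial is not given, and no rule covers the case where AIC and BIC disagree.

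The same section names the targets: "Primary effects of interest are groupXtime interactions from pre- to post, pre- to 3-month follow-up, and pre- to six month follow-up". By section 4 and the schedule in 7.2 these are weeks 12, 24 and 36. The multiplicity correction treats nine tests at post-test and three at the 6-month follow-up as distinct tests.

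A covariate is also settled by fit: "Models with and without social desirable responding will be compared and the best fitting model will be used". No social-desirability measure is listed in section 6 or in the 7.2 schedule.

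**The concern.** A confirmatory contrast should mean the same thing whatever the data turn out to be. Here the week-12 effect, and the claim that it persists to weeks 24 and 36, depend on which curve wins a comparison made on the trial's own outcomes and informed by plots that separate the arms. The reported p-value takes no account of that choice. Both co-primary outcomes and the claim of durability are exposed.

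The procedure also sits badly with the section's own targets. Two of the four candidate families have a single group-by-time parameter and so cannot tell an effect that fades from one that lasts.

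**Working it through.** **Inputs from the protocol.** N = 4,000 (8.1, 8.2), allocated 1:1 (7.1); eight assessments at weeks 0, 1, 3, 5, 8, 12, 24 and 36 (section 4, 7.2); r = .50, power 0.80 and alpha 0.006 (8.2: "We plan to test a total of 9 primary and secondary outcomes for a Bonferroni corrected error rate of 0.006"; 0.05/9 = 0.0056).

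**Assumptions of the check.** SD 1, complete data, equal correlation between visits, random-intercept maximum likelihood, log(1 + week) for the loglinear form, polynomials of degree 2 and 3, piecewise knot at week 12. The effect trajectories are also assumed.

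**1. The plan's own figure.** For the group-by-time F test, λ = f²Nm/(1 − r), with f = d/2 and df (m − 1) and (N − 2)(m − 1). At 80% power this gives d = 0.034 for m = 10 and 0.043 for m = 5. Rounded up, these are the stated 0.04 and 0.05 (with the eight scheduled assessments, 0.037). They refer to an omnibus interaction test, not to a contrast at one visit.

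**2. What each form does to the contrasts.** Let Δ(w) be the group difference in change from baseline to week w.
- Linear: Δ(w) = βw with standard error w·SE(β), so z = β/SE(β) at every w. Loglinear: Δ(w) = β·log(1 + w), and the factor cancels in the same way. In both there is one z and one p-value for weeks 12, 24 and 36.
- Piecewise: Δ(12) = 12β₁, Δ(24) = 12β₁ + 12β₂, Δ(36) = 12β₁ + 24β₂. Hence Δ(24) is forced to equal the mean of Δ(12) and Δ(36).
- Quadratic: two parameters for three contrasts. A cubic has three, but still has to fit all eight visits with one smooth curve.

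**3. Type I error at nominal 0.05, no arm difference at any visit** (simulation):

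| Situation | Wk 12 / 24 / 36 |
|---|---|
| Flat outcomes, AIC, candidates with group-by-time | .094 / .077 / .069 (repeat: .091 / .075 / .067) |
| Flat outcomes, BIC, same candidates | .069 at each (repeat: .066) |
| Both arms share a 0.1 SD trend | about .05 to .06 |
| Flat outcomes, curves compared without group terms | about .045 to .050 |
| Any single prespecified linear, log, quadratic or piecewise form | .048 to .050 |
| Categorical visits | .048 to .055 |

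Since every single prespecified form holds its level, the excess in the first two rows comes from selection.

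**4. Bias.** Each form was fitted by within-person least squares at the eight visit times to an assumed fast rise: differences of .10, .20, .23 and .25 SD at weeks 1, 3, 5 and 8, then .25/.22/.20 at weeks 12/24/36.

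| Form | Wk 12 / 24 / 36 (true .25 / .22 / .20) |
|---|---|
| Linear | .03 / .07 / .10 |
| Loglinear | .14 / .18 / .20 |
| Quadratic | .17 / .20 / .08 |
| Piecewise | .21 / .16 / .10 |
| Mean after selection, 2,000 per arm | about .24 / .16 / .16 |

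After selection the week-24 shortfall is (.22 − .16)/.22 = 27%.

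Other shapes give other answers:
- A straight ramp to .25 at week 12: almost no bias after selection.
- A ramp to .20 followed by a plateau: .198/.204/.201 with AIC but .185/.210/.223 with BIC, which picks the log form in 61% of runs.
- An effect of 0.2 SD at weeks 8–12 that is gone by week 24: the week-24 estimate is off by about 0.03 SD, and a true zero is rejected in 19% (AIC) or 21% (BIC) of runs.

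**5. Price of categorical visits.** The standard error of a contrast is √(4v/N). For the categorical change contrast v = 2(1 − r) = 1.00; with baseline adjustment v = 1 − r² = 0.75. For a correct prespecified piecewise model v = 0.638/0.401/0.576 at weeks 12/24/36. The detectable d is (2.748 + 0.842)·√(4v/4,000):

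| Model | Wk 12 | Wk 24 | Wk 36 |
|---|---|---|---|
| Correct piecewise | 0.091 | 0.072 | 0.086 |
| Categorical, unadjusted | 0.114 | 0.114 | 0.114 |
| Categorical, baseline-adjusted | 0.098 | 0.098 | 0.098 |

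The variance ratios to piecewise are 1.57/2.49/1.74 unadjusted and, with 0.75 in the numerator, 1.17/1.87/1.30 adjusted. Power for d = 0.10 at week 12 and alpha 0.006 is 0.89, 0.66 and 0.82 for the three rows.

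**The case against.** The best defence has four parts.

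- **Section 8.4 does not say that the compared curves contain group terms.** If only time curves common to both arms are compared, type I error stays at its nominal level. This stands, and it makes the inflation conditional. It does not remove the shape constraint on the contrasts.
- **The piecewise candidate separates intervention from follow-up, and contrasts that share parameters are still different contrasts.** This is true, so it would go too far to say that the plan cannot estimate its three effects. But nothing guarantees that the piecewise form is chosen.
- **At the planned size, selection discards the worst forms.** For three assumed trajectories through .25/.22/.20 at 2,000 per arm, linear was essentially never chosen, and the mean week-12 estimate was .23 to .26. Week 36 ranged from .15 to .22 against .20. This stands: the bias is usually modest and depends on shape.
- **Section 8.4 points to an external preregistration that may fix the form.** That cannot be checked here. If it does, the protocol text still describes something else and needs aligning.

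A reader might also infer more than the documents support. Fitting only a random intercept when correlation decays over time gives rejection rates well above 10%, but that reflects covariance misspecification, and section 8.4 does not commit to such a structure. At 1,000 per arm BIC can favour the log form in most runs (71% under one trajectory), but that is half the planned size. The gain from v = 1.00 to 0.75 applies to a saturated or two-visit contrast; it is not a fault in a curve model that uses all visits.

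**Conclusion.** The point holds in a limited form. As written, section 8.4 lets the confirmatory form of time depend on outcomes viewed by arm and on AIC/BIC, and two of its four candidate families collapse the three effects of interest into one test.

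The consequences are possible, not certain. Type I error is about 7–9% at nominal 5% if outcomes are flat and the candidates carry group-by-time terms, and near nominal otherwise. Bias runs from negligible to roughly a quarter of the effect at week 24 under the fast-rise trajectory. All these sizes rest on the assumed trajectories, polynomial degrees, equal correlation and complete data. The human reading of the loess plots and the covariate choice were not simulated, so no size is attached to them.

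It would be tempting to conclude that the plan inflates type I error outright, or that categorical visits cost nothing. Neither is supported: the first is conditional, and the second is contradicted by the precision figures. What remains is a cheap and worthwhile improvement to the primary analysis.

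**What to change.** - Prespecify one primary model: visit as a categorical factor, group-by-visit, unstructured within-person covariance, and baseline adjustment (baseline as a covariate, or baseline means constrained equal across arms).
- Tie the contrasts to the 7.2 schedule: weeks 12, 24 and 36 for distress, WHO-5 and the Maslach subscales; week 12 only for the Healthy Minds Index and GQ-6; weeks 12 and 24 for dried blood spots.
- Keep the loess plots and the AIC/BIC comparison as descriptive or secondary work on the shape of change.
- Decide in advance whether the social-desirability covariate is included, and if it is, state when it is measured.
- Align section 8.4 with the preregistration.

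The cost is wording and a few extra parameters, with no new data. There is some loss of precision against a piecewise model that happens to be right: with baseline adjustment, detectable d is 0.098 at each visit instead of 0.091, 0.072 and 0.086 at weeks 12, 24 and 36. That is affordable with 4,000 participants.

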#### **6.1.2 Secondary Outcomes**

Secondary Outcomes consist of: the Healthy Minds Index (17-items), a measure of four components of well-being – awareness, connection insight and purpose; Gratitude Questionnaire 6 (6-items); and the Maslach Burnout Inventory Emotional Exhaustion and Personal Accomplishment subscales (15-items).

Administrative records. We will receive prior, current and next year employment records on participants, including, number and reasons for absences and type of employment. Biomarkers - Dried blood spot substudy: CRP, IL-6, IL-10, TNFalpha.

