### **7.2 Schedule of Events**

| Event                                         | Prescreen | Baseline | Wk 1 | Wk 3 | Wk 5 | Wk 8 | Wk 12 | Wk 24 | Wk 36 |
|-----------------------------------------------|-----------|----------|------|------|------|------|-------|-------|-------|
| Screening and Stratification Measures  |           |          |      |      |      |      |       |       |       |
| Informed Consent                              |           | X        |      |      |      |      |       |       |       |
| Demographics                                  | X         | X        |      |      |      |      |       |       |       |
| Primary and Secondary Outcomes         |           |          |      |      |      |      |       |       |       |
| PROMIS Anxiety, Depression & Perceived Stress |           | X        | X    | X    | X    | X    | X     | X     | X     |
| WHO-5                                         |           | X        | X    | X    | X    | X    | X     | X     | X     |
| Healthy Minds Index                           |           | X        | X    |      | X    | X    | X     |       |       |
| GQ-6                                          |           | X        |      |      | X    | X    | X     |       |       |
| Maslach Burnout Inventory                     |           | X        |      |      |      | X    | X     | X     | X     |
| Dried blood spots                             |           | X        |      |      |      |      | X     | X     |       |
| Tertiary Outcomes (Mechanisms)         |           |          |      |      |      |      |       |       |       |
| FFMQ                                          |           | X        |      | X    |      | X    | X     |       |       |
| IRI- Empathic Concern                         |           | X        |      |      | X    | X    | X     |       |       |
| CERQ - Reappraisal                            |           | X        |      | X    | X    | X    | X     |       |       |
| ML- Presence                                  |           | X        | X    |      |      | X    | X     |       |       |
| MAIA Self-regulation                          |           | X        | X    | X    |      | X    | X     |       |       |
| CEAS                                          |           | X        |      |      |      | X    | X     |       |       |

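### Section 8.4 defines the effects as change from baseline by group and states no adjustment for the baseline value; on the usual reading this costs the biomarker contrasts about 20% of their information.

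*Protocol*

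**What the plan says.** Section 8.4 of the Protocol fixes three things.

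- **Model:** "Primary and secondary outcomes will be analyzed using linear mixed effects models with time nested within participant".
- **Effect:** "Primary effects of interest are groupXtime interactions from pre- to post, pre- to 3-month follow-up, and pre- to six month follow-up".
- **Adjustment:** "We will control for gender and age". A social-desirability score is added only if it improves fit.

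The shape of time is to be chosen by AIC and BIC among "candidate models of linear change, loglinear change, polynomial change, and piecewise linear change".

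Section 6.1.2 lists the biomarkers among the secondary outcomes: "Biomarkers - Dried blood spot substudy: CRP, IL-6, IL-10, TNFalpha". Section 4 says that "dried blood samples will be collected at baseline, week 12 and week 24", and the schedule in 7.2 agrees, so each analyte has one baseline value and two later ones. Section 8.2 also frames the biomarker power calculation as a group-by-time interaction, and assumes "A correlation of $r = .60$ between the same measure at different assessments". The value assumed for the survey measures is .50.

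**The concern.** Baseline enters this model as one of the outcome visits. If each arm has its own baseline mean, which is how group, time and their interaction are ordinarily fitted, the pre-to-post interaction subtracts each arm's baseline mean in full. With a correlation below 1, full subtraction over-corrects and carries the noise of a single baseline measurement into every contrast.

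Under randomisation the true baseline means are equal. A model that uses this, or that regresses the later value on the baseline value, estimates the same between-arm effect with smaller variance. At stake is precision, mainly in the blood-spot substudy, where numbers are small and each person has only three samples. The validity of the estimate is not in question.

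**Working it through.** **Inputs (Protocol 4, 7.1, 7.2, 8.2).** Correlation r = .60 for biomarkers and .50 for survey outcomes. Biomarker alpha 0.005 (taken as two-sided), power 0.90, d = 0.15, 468 participants, so 234 per arm at 1:1. Biomarker visits at weeks 0, 12 and 24. Co-primary visits at weeks 0, 1, 3, 5, 8, 12, 24 and 36.

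**The plan's own figure.** Take a repeated-measures interaction test with m = 3 visits, f = d/2 = 0.075 and noncentrality N·m·f²/(1-r). At N = 468 this is 468 × 3 × 0.005625 / 0.40 = 19.7. With 2 and 932 degrees of freedom and alpha 0.005, power is 0.905. The smallest even N that reaches 0.90 is 464. So 468 is reproduced to within 1%, but as a 2-df test over three visits, not as one pre-to-post contrast.

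**Two-visit contrast.** With equal variances, in SD² units per person:

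- difference in change: 2(1-r)
- baseline-adjusted difference: 1-r²
- ratio, adjusted to change: (1+r)/2

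| | r | Change | Adjusted | Ratio | Loss |
|---|---|---|---|---|---|
| Biomarkers | .60 | 0.80 | 0.64 | 0.80 | 20% |
| Survey outcomes | .50 | 1.00 | 0.75 | 0.75 | 25% |

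**Biomarker precision at 234 per arm.** SE = √(2v/234). For v = 0.80 it is 0.083 SD; for v = 0.64 it is 0.074 SD. The effect detectable with 90% power is (2.807 + 1.282) × SE, which is 0.338 against 0.302 SD.

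**Power at the planned effect.** Taking d = 0.15 as a between-arm difference in raw SD units:

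- change: 0.15/0.0827 = 1.81, power about 16%
- adjusted: 0.15/0.0740 = 2.03, power about 22%

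For 90% power the contrast would need 1,189 per arm by change or 951 per arm with adjustment.

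**Time shapes listed in 8.4.** Generalised least squares, assuming compound symmetry and complete data, compares separate baseline means with a common baseline mean. The table gives the share of information lost by the separate-means form. Quadratic stands for the polynomial candidate, and the piecewise knot is at week 12.

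| Time shape | Biomarkers, wk 12 and 24 | Co-primaries, wk 12 / 24 / 36 |
|---|---|---|
| Each visit free | 20% | 25 / 25 / 25% |
| Piecewise | 20% | 16 / 18 / 8% |
| Quadratic | 20% | 17 / 19 / 6% |
| Linear | 21% | 9 / 9 / 9% |
| Log-linear | 26% | 24 / 24 / 24% |

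**Scale for the co-primaries.** With about 2,000 per arm, even the two-visit case moves the SE only from √(2 × 1.00/2000) = 0.032 to √(2 × 0.75/2000) = 0.027 SD.

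**The case against.** The strongest reply is that section 8.4 never says the change is unadjusted. A model with a common baseline mean also expresses its effects as group-by-time terms, so the stated effect is compatible with the efficient model, and the section refers to a preregistered plan that is not shown. This stands in part: the separate-means reading is the ordinary one, not a stated one. But the protocol does name its effect and its covariates, and as written they leave the baseline value out, so more is involved than a detail left to another document.

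Other points that stand:

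- A reader might infer that the co-primaries lose a flat 25%. That holds only for a single pair of visits or when every visit is free. Section 8.4 lists smoother time curves over eight visits, where the loss can be as low as 6%.
- A reader might infer bias. There is none: the interaction is a valid randomised comparison.
- A reader might infer that adjustment would make the substudy adequately powered. At d = 0.15 on the raw SD scale it does not.
- The gain is less secure for the blood spots. Section 4 puts baseline assessments before randomisation, but 8.2 selects 255 from each group and expects 10% to give no pre-test sample. Selection, and perhaps the first spot, may therefore follow allocation.
- Section 8.4 counts seven secondary tests. The four Healthy Minds components, gratitude and two burnout subscales already make seven, so the biomarkers may have analysis details elsewhere. Section 6.1.2 nevertheless lists them as secondary, and 8.4 applies its model to secondary outcomes.

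**Conclusion.** The point holds as one of efficiency. On the usual reading of 8.4, the biomarker contrasts lose about 20% of their information at the plan's r = .60, and 20-26% across the listed time shapes. Keeping the change contrast at its present size is equivalent to giving up 1/0.80 = 1.25, or 25% more participants. For the co-primaries the loss is about 6-25%, depending on time shape and visit, with little practical effect at up to 4,000 participants.

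These figures assume equal variances over time, the plan's correlations at every pair of visits, complete data, and a model with separate baseline means. If a common baseline mean is already intended, there is no loss and one clarifying sentence settles the matter.

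**What to change.** In 8.4, define the post-baseline effects as baseline-adjusted between-arm differences, in one of two forms:

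1. the mixed model with a common baseline mean for both arms and group-by-time terms only after baseline; or
2. post-baseline values as outcomes, with the baseline value as a covariate.

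The first form keeps participants who lack a baseline sample. For the blood spots, use it only if the baseline spot is taken before allocation is known; otherwise use the second form. State in the protocol which order applies.

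The cost is a sentence and a changed model statement, with no new samples, visits or participants. Timing needs care. Recruitment was to close on May 21, 2023; 36 weeks from then ends in late January 2024, and version 1.1 is dated 12.20.2024. If the data have already been seen, report the adjusted analysis as a labelled change alongside the preregistered contrast, not in its place.
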